### Secondary Outcome Measures

The secondary outcomes for the study will further describe uptake of HTC in the intervention and control groups. In particular, we will compare the following outcomes between the two study groups:

Discussions about and uptake of HIV testing:

- Proportion of participants who report that they discussed HIV testing with their partner;
- Proportion of participants whose partners undergo HIV testing individually (partner testing);
- Proportion of participants who undergo couples HIV testing with their partners;

In accordance with WHO guidelines, we define partner testing as a scenario in which one partner (for example, women who participate in our study) has already tested and the other partner (the primary sexual partner of the women) is tested separately without mutual disclosure of HIV status necessarily occurring. On the other hand, couples testing is defined as a scenario in which both partners are counselled, tested, and provided with their results together so that mutual disclosure of HIV status occurs.

Actions taken after HIV testing:

- Sexual behavior and decision making (such as condom use) after HIV-positive and HIV-negative test results for partners;
- Adverse reaction to a positive or discordant result

Since confirmatory testing is recommended following the use of HIV self-tests, in the intervention groupwe will also measure *use of confirmatory testing*by individuals who were reported to have used the self-tests. Participants will be given referral vouchers for confirmatory testing at several VCT clinics in Kisumu so that this can be recorded. We will also obtain self-reported information from the study participants about whether each person who used the self-test sought confirmatory testing.

We will also describe several aspects of self-test usage (where it takes place, how often women suggest the self-test usage to their partners, what reactions male partners have to self-test, etc.).During the follow-up interview we will ask to see the used self-testing package if study participants report that they or their male partner used the self-test.

We will also report outcomes related to social harms, such as experiences of IPVand increase in unprotected sex, if they occur.

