# JUSTIFICATION

The proposed intervention helps overcome many of the barriers to uptake of facility-based HTC among men such as reluctance to visit healthcare facilities, stigma, and costs such as transportation and lost wages. The intervention leverages the advantages of self-tests – greater privacy and ease of use – while also using the female partners of men to advocate for HIV testing rather than other ways to promote testing among men that may be less effective. In the proposed intervention, women will be given two HIV self-tests and encouraged to either provide one self-test to their male partner for own use (partner testing) or to use the two tests together with their partners (couples testing). Since self-tests have advantages over facility-based HTC, the pilot intervention we will implement has the potential to achieve higher uptake of HIV testing among male partners than the current standard of care that encourages pregnant and post-partum women to refer their partners for HTC at fixed sites. The impact evaluation of the pilot intervention will use a randomized trial design to assess the effect of the intervention relative to the standard of care. Outcomes studied will include uptake of HIV testing among male partners, uptake of couples testing, reported adverse events, and linkage to care.

Our rationale for providing multiple self-tests to pregnant and postpartum women attending antenatal and postpartum clinics also lies in the special importance of partner or couples testing taking place in this population.Women have ongoing risk of acquiring HIV in pregnancy and postpartum [35]. Due to elevated risks of HIV transmission (female-to-male) and acquisition (male-to-female) during pregnancy – as well as the greater risk of maternal-to-child transmission if women have higher viral loads as a result of becoming newly infected during pregnancy or postpartum – it is particularly important that partners of pregnant women receive HTC. In fact, partner and couples HTC has been strongly endorsed by the WHO and fairly widely promoted in antenatal care settings [11]. The key challenge however, has been in promoting widespread *uptake* of either partner or couples testing in ANC settings. In most countries including Kenya only a small proportion of male partners attend ANC or postpartum clinics (PPC) with their partners and get tested with them [12, 36].

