## Sampling

Research Assistants (RAs) will invite eligible individuals to participate in the study.Recruitment of participants will take place at the Lumumba Health Centre in Kisumu, Kisumu East District Hospital and Rabuor Health center. Staff at the ANC and PPC clinics will inform patients as they are being discharged home that there is a study they may qualify for; if they express interest in learning more, they will be given a referral coupon to take to the study staff based at the facility. For ANC and PPC patients, the referral coupons will be identical and will have a unique number rather than the women’s names or any other identifying information. Before issuing the coupon to women, the ANC and PPC staff will write down a discreet code for whether the woman is HIV-positive or HIV-negative (OP for HIV-positive and ON for HIV-negative). Only the study and clinic staff will know what the codes denote. We believe the coding system will be discreet enough to not disclose the HIV status to unauthorized person(s). This information will be necessary for assessing participation rates in the study by HIV-positive and HIV-negative women, analyzing use of self-testing by HIV status, and for sampling HIV-positive and HIV-negative participants in qualitative interviews. Once the RAs collect the referral coupons from the women, the number on the coupon and the HIV status code on the coupon will be recorded on secure tablets. No identifying information will be collected for women who decline to participate in the study.

Women at all stages of pregnancy and post-partum care will be referred to study RAs. The study RAs will then explain the study to women, screen them for eligibility for the study, and ask those who are eligible if they are willing to participate in the study. RAs will obtain informed consent and enroll the woman into the study. We will conduct recruitment in the study facilities in a manner that ensures the number of participants in each facility is proportional to the number of women who seek care at each facility.

During the qualitative phase of the study, we will purposively sample a sub-set of about 45 study participants. We will seek to include 10-15 women who tested together with their partners (couples testing), 10-15 women who gave the test to their partner to use (partner testing), and 10-15 women who never used the test or gave it to their partner to use.We will sample from among all study sites and both ANC and PPC clients.

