**Intervention group**

Participants in the intervention group will be given clear, accessible instructions on how to use the tests (this will be communicated to them and provided on a written document). Participants will be instructed to call a phone hotline that we will establish in the event of any adverse events that they or their sexual partners experience. They willalso be given a list of places that partners can access for confirmatory testing and advisedto encourage their partner to go for confirmatory testing.

They will be also receive information about HIV self-testing including reasons for suggesting usage of the self-test to their partner and strategies for introducing self-tests to their partners; however, it will also be emphasized that women are under no obligation to suggest to their partner or convince him to use the self-test. Because use of self-tests at home will mean that a trained counselor will not be present when women or their partners take the test, we will develop messages that can be communicated to women easily so that they and their partners can use the self-tests correctly and safely on their own. The messages and counseling that we will provide will adhere to Kenya’s National Guidelines for HIV Testing and Counseling [16].

Two self-test kits will then be distributed to women, each containing the following:

- One standard OraQuick ADVANCE I/II test kit with developer fluid vial and stand;
- Written pre-test information including test instructions in written and pictorial form, post-test counselling information and details about how and where to access HIV confirmatory testing in or near Kisumu;
- Aphone number that participants can call to obtain additional information about taking the test, interpreting results, obtaining referral information,post-test counseling or obtain help in case of IPV.
- Two voucherswith unique identifying numbers which can be redeemed at confirmatory testing for a small token.

All the information above will be communicated orally to women initially and also provided in written form ofan information sheet, in English, Kiswahili and Luo.

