**Follow-up interviews**

Follow-up interviews with participants in the control and intervention groups will be conducted by trained counselors 3 months after enrollment in order to learn about decision-making regarding partner or couples testing. In the control group, we will obtain information from participants on whether they asked their partner to accompany them to the ANC and use the referral voucher for voluntary HTC. In the intervention group, we will obtain information from participants on whether they suggested usage of the self-test to their partner, whether their partner used the self-test, and whether the couple used self-tests together (with mutual disclosure of HIV status) or if instead the partner was believed to have used the self-test alone. In cases where self-tests were reported to have been used, trained HTC counselors will also ask to see the self-tests and obtain visual confirmation of usage. We will also obtain self-reported information on whether partners who used self-tests sought confirmatory testing (those who did not but wish to have their results confirmed during the visit will be tested by the counselor) and whether partners who obtained an HIV-positive test result sought care at an HIV clinic.

In both groups, we will ask participants whether their partners have accompanied them for ANC or PPC visits in the past 3 months. We will also ask participants if their partners have sought care at an HIV clinic in case an HIV-positive test result was obtained. Finally, in both groups, we will inquire about adverse eventssuch as reports of verbal abuse or physical violenceduring the follow-up interview; those who report events will be referred for support. The study will provide a 24-hour hotline that participants can call with questions or to report an adverse event. The hotline will be staffed by trained study personnel who will be available to counsel and provide referrals to participants. If any adverse events are reported, they will immediately be reported to the Ethical Review Boards and action will be taken where possible.

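### Couples testing, a between-arm secondary outcome, is formally defined to include joint counselling, but elsewhere joint unsupervised kit use counts, and the two arms are measured by different methods

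*Protocol*

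**What the plan says.** Secondary Outcome Measures announces that "we will compare the following outcomes between the two study groups" and includes "Proportion of participants who undergo couples HIV testing with their partners" in the list. Citing WHO guidelines, it then states that "couples testing is defined as a scenario in which both partners are counselled, tested, and provided with their results together", with mutual disclosure as the result. Partner testing is defined there as the male partner being tested separately, with disclosure not required.

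Other sections use the couples label without a counselling element:

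- **Justification:** as an alternative to handing over one kit, women are encouraged "to use the two tests together with their partners (couples testing".
- **Sampling:** the qualitative sample is to include "10-15 women who tested together with their partners (couples testing".
- **Follow-up interviews, intervention arm:** women are asked "whether the couple used self-tests together (with mutual disclosure of HIV status", or whether the partner is thought to have used a kit alone.

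The Intervention group section acknowledges that "a trained counselor will not be present when women or their partners take the test". Each kit does contain "Written pre-test information including test instructions in written and pictorial form, post-test counselling information" and a phone number through which post-test counselling can be obtained.

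For controls, the section on recording uptake of voluntary HTC says that individual or couple attendance will be determined from vouchers presented at HTC sites. Those vouchers can be used at a facility of the couple's choice, but the research assistants who record them are named only at the three study facilities.

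**The concern.** Joint use of two kits is one of the two uses that the intervention promotes. If the outcome meant to capture it requires joint counselling, and the kits are used without a counsellor, the formal definition and the intervention do not fit together. An analyst who follows Secondary Outcome Measures and one who follows Follow-up interviews could report different intervention proportions from the same data.

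Separately, the arms are not measured alike, so a difference between them could partly reflect the method of measurement. Couples testing is part of the stated objective (partner or couples testing), and the protocol plans logistic regression for the secondary outcomes. The result would therefore appear as a formal treatment comparison.

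**Working it through.** **1. The plan's own figure.** The only relevant figure is under Sample size justification: 80% power with 300 women per arm for 20% v 30%. With two-sided alpha 0.05 and a normal approximation without continuity correction:

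- standard error under the null = sqrt(2 x 0.25 x 0.75 / 300) = 0.03536
- standard error under the alternative = sqrt((0.20 x 0.80 + 0.30 x 0.70) / 300) = 0.03512
- z = (0.10 - 1.96 x 0.03536) / 0.03512 = 0.874, which gives power of 80.9%.

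The figure reproduces. It concerns partner or couples testing combined, so it says nothing about couples testing alone, for which no rate is given.

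**2. The texts side by side.**

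| Section | Joint counselling required? | Mutual disclosure required? | Source of data |
|---|---|---|---|
| Secondary Outcome Measures (formal definition) | Yes | Yes | Not stated |
| Justification; Sampling | No | Not stated | Not stated |
| Follow-up interviews, intervention arm | No | Yes | Woman's report |
| Recording uptake, control arm | Not recorded | Not recorded | Vouchers presented |

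Two things follow.

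- *Definition.* A couple who use both kits together at home and share results meet the Follow-up interviews description but, read literally, not the formal one. Nor do they meet the formal definition of partner testing, because they were not tested separately. Under Secondary Outcome Measures they are unclassified.
- *Measurement.* A presented voucher does not show that results were shared, so control couples can be counted without disclosure. A control couple who test together at a facility outside the three may not be recorded at all. These errors act in opposite directions, and neither arises in the same way in the intervention arm.

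**3. The common self-report item.** Limitations recognises the arm-specific measurement and adds one question for both arms: whether the partner tested by any route after enrolment. It does not ask whether the couple tested together. The control-arm questions described under Follow-up interviews cover asking the partner to attend and use the voucher, and his accompanying her to visits. They do not cover joint testing. The follow-up questionnaire itself is an appendix that is not reproduced.

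**4. Size, by assumption.** Assume control couples testing of 5%, 10% or 15% (15, 30 or 45 of 300) and joint home use of 20% to 30% in the intervention arm (60 to 90 of 300). Difference = intervention minus control, in percentage points.

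| Control | Strict, no facility couples testing in the intervention arm (0%) | Strict, 5% facility couples testing in the intervention arm | Joint home use counted (20% to 30%) |
|---|---|---|---|
| 5% | 0 - 5 = -5 | 5 - 5 = 0 | 20 - 5 = +15 to 30 - 5 = +25 |
| 10% | 0 - 10 = -10 | 5 - 10 = -5 | 20 - 10 = +10 to 30 - 10 = +20 |
| 15% | 0 - 15 = -15 | 5 - 15 = -10 | 20 - 15 = +5 to 30 - 15 = +15 |

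Over these assumed ranges, the choice of reading can change the sign.

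**The case against.** A reader might infer that the intervention proportion is zero by construction. The protocol does not support that. The section on utilization of confirmatory testing gives intervention women vouchers that they and their partners can use at a facility, where a couple could be counselled and tested together. The kits also supply written counselling material and a counselling phone line, and the formal definition does not say that a provider must be present at the test. What stands is narrower: the protocol never says that written or phone counselling amounts to being counselled together, and no follow-up item described in it would record this.

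A reader might also infer that joint self-testers would be moved into partner testing. That does not follow either, because partner testing requires the partner to be tested separately.

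The strongest objection is that the intent is plain. The Justification, Sampling and qualitative sections all separate joint use from use by the partner alone, so a sensible analyst would count joint kit use. That is probably right, and it makes the strict figures an outer bound rather than a forecast. But the only formal definition is the one with counselling in it, and counting joint kit use does not cure the difference in measurement.

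Finally, the Follow-up data list gives both couples testing and reported mutual disclosure for each group, and the design overview has controls asked at 3 months whether they or their partners sought testing. Reported disclosure is thus planned in both arms, which makes the fix easier. It does not override the control-arm text, which decides couple attendance from vouchers.

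**Conclusion.** The concern holds as an unreconciled definition combined with arm-specific measurement of a named secondary outcome. It is not a structural zero. Its size cannot be derived from the protocol. The illustrative range of -15 to +25 points rests on three assumptions: control couples testing of 5% to 15%; joint home use of 20% to 30%; and, at the negative end, no couples testing at facilities in the intervention arm with written or phone counselling not counted. The contradiction between sections and the difference in data source need none of these assumptions.

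The primary outcome, hypothesis and power calculation concern any partner testing and do not depend on how couples and partner testing are split. The point should be corrected, but it does not threaten the main conclusion.

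**What to change.** Use one arm-neutral definition throughout. Couples testing means that both partners were tested for HIV on the same occasion within 3 months of enrolment, by any modality, and each learned the other's result. Partner testing means that the partner was tested within 3 months but this definition was not met, so that every tested partner falls into exactly one category.

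Establish both by the same follow-up questions in both arms, and keep voucher records as supporting verification. Report the presence of a counsellor descriptively. Align Secondary Outcome Measures, Follow-up interviews and the control-arm recording section with this text.

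The cost is some rewording and one common follow-up item. There are two downsides: the definition departs from the cited guideline wording, which should be stated, and the outcome then rests on self-report in both arms.

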### QualitativeSub-Study

In addition, a qualitative sub-study focused on women in the intervention group will provide additional details on the usage of self-tests for promoting partner or couples HIV testing. We will conduct in-depth interviews with participants and explore in-depth the process of making a decision to suggest use of the self-test with a sexual partner; the reactions of sexual partners; the experience of using the test with a sexual partner; and decisions made after using the self-test, including sexual behavior decisions, experiences of violence or coercion, uptake of confirmatory testing, and linkage to care.

# STUDY DESIGN

## Overview of study design

To determine the impact of the intervention on partner or couples HIV testing, the project will use a randomized controlled trial design.

We will recruit about 600 adult womenfrom antenatal and postpartum careclinics. Participants will be randomized to one of two groups: intervention or control.

Following a baseline interview, participants in the intervention groupwill be shownhow to correctly use theself-tests and given two HIV self-tests. Subsequently, we will contact participants periodically over a 3 month period to see if they have used the test(s) with their sexual partners and conduct a follow-up interview.

Following the baseline interview, participants in the control group will be given referral vouchers for themselves and their partners to obtain HIV testing at VCT centers. We will contact the participants at the end of 3 months to see if they and/or their partner(s) have sought HIV testing.

We will also conduct in-depth qualitative interviews with a subset of study participants in the intervention group, including participants who have used HIV self-tests together with their partner, those who have used the test [partner testing] and those who have not used HIV self-tests.

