### Primary Outcome Measures

The primary outcome for the study will be uptake of HIV testing by women’s partnerswithin 3 months of enrollment in the study. For each participant, we will record whether the participant’s partner underwent HIV testing – in the case of the intervention group, this will be a report by female study participants that their partner used a self-test; in the control group, this will be uptake of HTC at the VCT by the partner. We will test for differences in the primary outcome variable between the intervention and control group.

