## Procedures

The intervention will consist of providing multiple HIV self-tests to women attending an ANC or post-partum clinic (PPC) in the city of Kisumu and its environs, providing information to them on how to use the self-tests and where to go for confirmatory testing and care if necessary, and then encouraging them totalk to their partner about self-testing and ask their partner to use the self-test (either independently or together).

The effect of this strategy on uptake of HIV testing among male partners will be compared with the current standard of care in which women are encouraged to refer their partner for HTC. After a 3 month period, we will obtain information from the women on the receptivity of their sexual partner to self-testing, whether they were able to use self-tests with their partner jointly or independently, and the incidence of any adverse events; participants will be encouraged to report any adverse event as soon as it occurs. Uptake of partnerHIV testing will be compared between self-testing and provider-based testing. We will also record whether the women’s partners seek confirmatory testing and link to care if an HIV-positive test result is reported to be obtained.

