**Recording uptake of voluntary HTC (control group)**

At the time of enrollment participants in the control group will be provided with referral vouchers (with a unique participant ID code) for HTC (at LHC or another facility of their choice within and around Kisumu) that they and their partners can use for either partner testing (partner tests alone) or couples testing. In the 3 months after enrollment, we will be able to clearly determine whether participants’ partners came for HTC either individually or as a couple based on whether the referral vouchers were presented at HTC sites.

Research assistants at LHC, KEDH and Rabuor Health Centrewill collect and record the referral voucher numbers (with a unique participant ID code) presented at the HTC sites when an individual comes for HIV testing. They will record whether participants’ partners presented these vouchers in the 3 months after enrollment in order to obtain information on utilization of testing by both intervention and control groups. This strategy has been successfully implemented in previous studies that our team has conducted in the Nyanza region of Kenya, including impact evaluations supported by the Gates Foundation and 3ie in which we record uptake based on presentation of referral vouchers.

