# LIMITATIONS

This study has several limitations that warrant discussion. We recognize the limitations of relying on self-reported HIV testing as an outcome variable. This is an inherent issue in all studies to date that have measured the use of self-tests, since the self-tests are typically used in private. We will take several steps to overcome the limitations of having self-reported outcomes in the intervention group and an objective outcome in the control group. First, in the intervention group, during the follow-up interview we will ask to see the used self-testing package in cases where study participants report that they or their male partner used the self-test (this has previously been done in other studies in Malawi). While the verification of used self-testing packages is not necessarily a flawless measure of actual usage of self-testing, it will provide some indication of how much higher the self-reported measure is relative to the verified measure. Second, we will also explore ways to verify whether the participants’ partner sought confirmatory testing after using the self-test: If the participant states that their partner went for a confirmatory test, we will check whether the referral voucher given to them were recorded at the VCT that they visited.

In comparing the intervention and control groups, we will also examine a self-reported outcome that will be similar in both study arms so as the reduce bias in the estimated effect of the intervention: in particular, we will ask study participants in both groups to self-report whether or not their partner tested for HIV through any modality after enrollment in the study (either in clinic or with self-testing). By virtue of being self-reported and comparable in both study arms, this will enable us to determine if the intervention resulted in higher reported HIV testing for ther partners of study participants. We believe that when we triangulate all this information, we will be able to make a more accurate determination of whether the intervention is effective in promoting HIV testing.

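### Intervention women are contacted periodically about kit use while controls are contacted only at 3 months, an unequal schedule that other sections do not describe and that may raise woman-reported outcomes in one arm

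*Protocol*

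**What the plan says.** The Protocol's Overview of study design sets the contact schedule separately by arm, in adjacent paragraphs. For the intervention group: "we will contact participants periodically over a 3 month period to see if they have used the test(s) with their sexual partners", followed by a follow-up interview. For the control group: "We will contact the participants at the end of 3 months to see if they and/or their partner(s) have sought HIV testing". The number, spacing, mode and script of the periodic contacts are not given.

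The detailed sections differ. Follow-up interviews covers both groups and says that the interviews "will be conducted by trained counselors 3 months after enrollment in order to learn about decision-making"; it lists no interim contact for either arm. Procedures likewise has information obtained from the women after a 3-month period. Justification and Procedures define what is being tested as kits, information and encouragement to involve the partner. Neither lists later study contacts.

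The primary outcome has a different source in each arm. In the intervention arm, "this will be a report by female study participants that their partner used a self-test". For controls, it is the partner's attendance for testing at a VCT site. Vouchers are logged at the facilities throughout, with staff noting whether partners "presented these vouchers in the 3 months after enrollment in order to obtain information on utilization of testing by both intervention and control groups". Limitations acknowledges that self-report in one arm is set against an objective record in the other, and adds a common measure: "we will ask study participants in both groups to self-report whether or not their partner tested for HIV through any modality". It does not mention contact frequency.

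**The concern.** Asking a woman several times whether she has used the kits with her partner may remind her to do so. It also gives her more than one occasion to say that he did. If only one arm is asked, the comparison is no longer kits and enrolment counselling against referral vouchers. It becomes kits, counselling and repeated study contact against vouchers with no interim contact.

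Three things are at stake:

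- **Attribution.** The dissemination section offers the result to the health ministry as evidence on self-tests. A programme that hands out kits without follow-up contact might not see the same uptake.
- **Woman-reported outcomes.** The intervention arm's primary outcome is the woman's report. The common self-report is the Protocol's safeguard against unequal measurement, but women already questioned about kit use would not answer it on quite the same terms as controls.
- **Harms.** Whether violence increases is a stated reason for the trial, and adverse events are to be compared between arms. Extra contact in one arm gives extra openings to disclose.

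Analysis cannot remove a difference in contact once follow-up has taken place.

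**Working it through.** **Step 1. Set the sections side by side.**

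| Protocol section | Intervention | Control |
|---|---|---|
| Overview of study design | Periodic contact about kit use over 3 months, then an interview | One contact at the end of 3 months |
| Procedures | Information from women after 3 months | No interim contact described |
| Follow-up interviews | One interview at 3 months | One interview at 3 months |
| Primary Outcome Measures | Woman's report of self-test use | Partner's uptake at the VCT |
| Recording uptake of voluntary HTC | – | Vouchers logged over the 3 months |
| Limitations | Any-modality self-report | Same question |

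Only the Overview mentions interim contact, and only for one arm. No section gives controls an interim contact. The sections therefore leave open whether the contacts will happen and whether they count as treatment.

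**Step 2. Which outcomes could be affected?** Those that come from the woman: intervention self-test use, discussion of testing, the common self-report and violence. The control arm's primary outcome is logged from vouchers, so its capture does not depend on how often the woman is contacted.

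**Step 3. Reproduce the stated power.** Inputs from Sample size justification: control 20%, intervention 30%, 300 per arm, 80% power. Two-sided 5% is stated in Statistical analysis for all other tests and is assumed here for the primary test. With d = p2 − p1 and p̄ the mean of p1 and p2:

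power = Φ{[d − 1.96 √(2p̄(1−p̄)/n)] / √([p1(1−p1) + p2(1−p2)]/n)}

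For 20% v 30%: p̄ = 0.25; 1.96 × √(0.375/300) = 0.0693; √(0.37/300) = 0.0351. So (0.10 − 0.0693)/0.0351 = 0.874, and Φ = 80.9%. The stated 80% reproduces.

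**Step 4. Illustrate the effect on attribution.** The Protocol gives no size for a contact effect. Assume that b of the planned 10 points come from contact, that effects add, and that the control rate stays at 20%. The kit effect alone is then 10 − b points.

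| b (assumed, points) | Kit effect alone | Comparison | Power, 300 per arm |
|---|---|---|---|
| 0 | 10 | 20% v 30% | 80.9% |
| 1 | 9 | 20% v 29% | 72.8% |
| 2 | 8 | 20% v 28% | 63.1% |
| 3 | 7 | 20% v 27% | 52.5% |
| 5 | 5 | 20% v 25% | 31.1% |

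Worked row, b = 3: p̄ = 0.235; 1.96 × √(0.35955/300) = 0.0679; √(0.3571/300) = 0.0345; (0.07 − 0.0679)/0.0345 = 0.06; Φ = 52.5%.

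Worked row, b = 5: p̄ = 0.225; 1.96 × √(0.34875/300) = 0.0668; √(0.3475/300) = 0.0340; (0.05 − 0.0668)/0.0340 = −0.49; Φ = 31.1%.

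No design effect or dropout is applied. Equalising contact would not change the planned sample size.

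**The case against.** The strongest reply is that one overview sentence is being read as the operative procedure. Follow-up interviews, the detailed section, has a single 3-month interview in both arms, and the periodic contacts have no stated number, mode or script. They are described as checks on use, not reminders. This stands in part: the text does not establish that prompting will occur. It leaves a conflict to be resolved, and the Overview wording would produce unequal contact if staff followed it.

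Second, a reader might infer that the intervention arm simply has more chances to record primary-outcome events than the control arm. The documents do not support that in general. Control uptake is logged from vouchers throughout, and intervention use is a cumulative question that the 3-month interview would cover anyway. What remains is a possible effect on reporting within the intervention arm.

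Third, on harms, the Protocol asks about adverse events in both groups at 3 months and describes a 24-hour hotline for participants, and the stated purpose of the interim contacts is test use, not violence. That limits the imbalance. It does not remove it, because any contact is an opportunity to disclose.

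Fourth, encouragement is already part of the intervention, and controls receive a token for testing itself, whereas the intervention arm's token is tied to confirmatory testing. The net direction of all non-kit differences is therefore not shown. This also stands, but enrolment encouragement is listed as part of the strategy and repeated later contact is not.

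**Conclusion.** The point holds as an inconsistency with a likely direction and an unknown size. The Overview of study design gives the arms different contact schedules, the detailed sections do not, and the definition of the intervention does not include the contacts. If the Overview is followed, repeated questions about kit use may raise reported use in the intervention arm, and they make the common self-report and the harms comparison less even. Voucher capture in the control arm is unaffected.

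The figures of about 53% and 31% power for the kit effect alone rest on an assumed 3 or 5 points from contact, additive effects and a 20% control rate. They show how sensitive attribution is and do not estimate bias.

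Two stronger readings should be resisted. A reader might infer an inflated false-positive rate: with no kit effect, 3 to 5 points from contact would give a significant result in favour of the intervention in 14.3% to 31.1% of trials. The arithmetic is right, but the intervention outcome counts only self-test use, so contact acts through the kits and this is not a true false-positive rate. A reader might also infer that retention will differ by arm. That could happen, but nothing in the Protocol shows that it will.

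**What to change.** Reconcile the Overview of study design with Procedures and Follow-up interviews, in one of two ways:

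- drop the interim kit-use contacts; or
- use the same number, timing and neutral script of contacts in both arms, without mentioning kits or vouchers.

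Keep the hotline for all participants in either case. State that woman-reported outcomes used to compare the arms, or to count intervention self-test use, come from the same 3-month interview. These include the any-modality report and intimate partner violence.

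Leave voucher recording unchanged. Taking the whole primary outcome from the interview in both arms would replace the voucher-based control endpoint, which is a separate and larger change that this point does not require.

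The cost is a revised sentence or two and, if contacts are kept, a common script. The downside is that interim kit-use information is lost, or that controls receive a few short calls beyond the standard of care.
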